### Randomization

After consenting to participate in the trial, we will use simple randomization to assign organizations to receive either the 'full-serve' or the 'self-serve' evidence service. The list of participating organizations will be sent to a statistician (TB) who will assign a unique ID number to each organization, conduct the randomization, and keep both the key linking the organizations to their ID and the randomization log in a secure password protected folder at the Ontario HIV Treatment Network to provide a clear audit trail. We will perform simple randomization sampling using the SAS SELECTSURVEY procedure to assign equal numbers of organizations to the 'full-serve' and the 'self-serve' groups. The procedure will be performed with a fixed seed so that the sampling can be replicated if needed. The statistician will then provide the list of unique IDs with the results of the randomization to the SHARE database administrator at the Ontario HIV Treatment Network (external to the research team) who will provide individuals from each participating organization with access to the 'full-serve' or 'self-serve' versions of SHARE. This will require the SHARE database administrator to have access to the key linking the unique IDs to the organizations but it will remain concealed from the research team.

Prior to the start of the trial, all organizations will be requested to provide a list of emails of management and staff interested in receiving access to SHARE, which will be provided to the SHARE database administrator at the Ontario HIV Treatment Network. We will then send bi-monthly emails to the executive director (or another delegated staff member for correspondence) to identify any staff that have either joined or left the organization in order to accurately track usage at the organizational level. The SHARE database administrator at the Ontario HIV Treatment Network will send the updates to individuals affiliated with organizations with access to the 'full-serve' version of SHARE (the updates will be written by [name] and checked by the co-investigators). The statistician (TB) is a member of the study team but will only be involved with randomization at the start of the trial and the data analysis upon completion of the trial. Therefore, participants and all investigators except the statistician (TB) and the SHARE database administrator will be blinded to group assignment.

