## Methods/design

We will conduct this trial using a sequential explanatory mixed methods design [25], beginning with the two-arm randomized controlled trial (RCT), and then following up with a qualitative process study to explore the RCT findings in greater depth. The trial will run for 10 months, which includes a two-month baseline period where all participants receive the 'self-serve' evidence service, a six-month period where the intervention group will receive the 'full-serve' evidence service and the control group will continue to receive the 'self-serve' evidence service, and a final two-month period where both groups will receive the 'full-serve' version of SHARE.

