## RCT methods and design

### Study population and recruitment

Community-based HIV/AIDS organizations in Canada provide a number of programs and services to people living with or affected by HIV, which may include prevention initiatives, individual or group counseling/support, and community outreach and/or education. In addition, organizations in Canada are situated in diverse geographic settings ranging from dense urban settings to rural, northern, and/or remote settings, with some focused on specific at-risk populations and/or cultural or ethnic groups.

We will draw our sample from those organizations affiliated with the Canadian AIDS Society and from relevant provincial HIV/AIDS networks (*e.g.*, the Ontario AIDS Network), and send an organizational invitation to the executive director and management team (if applicable). The invitation will indicate that if they are interested in having their organization participate, access to SHARE will be provided to all interested staff. Given that SHARE is currently only provided in English, we will exclude organizations that do not have at least one key decision maker who is comfortable participating and corresponding in English.

To ensure clarity in our study recruitment, we will outline that consent from the executive director is required for the organization to participate. We will also indicate that we require one key organizational decision maker to fill out a brief survey measuring their intention to use research evidence (see the Outcomes section for more detail on the survey) on behalf of their organization at baseline and again at the completion of the trial. We will request that the executive director complete the survey, but will indicate that they can delegate to another manager provided the manager has a decision-making role about programs, services, and advocacy, and provided the manager does not include the conduct of research among their core responsibilities. Because the overall intent of the intervention is to support the use of research evidence in decisions about CBOs' programs, services, and advocacy, we deemed it most appropriate for the executive director (or another manager) to complete the survey because they would have the most impact on whether research evidence is used to inform decisions.

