Using a manual to support health researchers who want to construct measures based on the theory [41], our colleagues have developed and sought preliminary feedback on a data-collection instrument by first assessing face validity through interviews with key informants and then pilot testing it with 28 policymakers and researchers from 20 low- and middle-income countries who completed it after participating in a KT intervention [48]. In addition, Boyko *et al*. (2010) found moderate test-retest reliability of the instrument using Generalizability Theory (G = 0.50) [49] when scores from a sample of 37 health system policymakers, managers, professionals, citizens/consumers, and researchers participating in stakeholder dialogues convened by the McMaster Health Forum were generalized across a single administration, and even stronger reliability (G = 0.9) when scores were generalized across the average of two administrations of the tool [48]. In the reliability assessment by Boyko *et al*. (2010), the first administration of the tool immediately followed a McMaster Health Forum stakeholder dialogue, which may have promoted enthusiasm for using research evidence among participants. This likely produced higher measures of intention on the first administration of the tool as compared to the second, resulting in the lower G-score. Given that we won't be administering the tool in a similar atmosphere of enthusiasm for using research evidence, it is likely that the level of reliability of the tool will be sufficient without two administrations at both baseline and follow-up.

We have slightly modified the wording in each of the questions of the tool to reflect the different intervention being tested (SHARE) and the target audience (CBOs) (see Additional file 3: Appendix 3). We will administer the instrument to one key decision maker from each organization during the baseline period, as well as at the end of the six-month intervention period, through a brief online survey that takes approximately 10 minutes to complete. We will use unique identifiers for each participant to ensure their responses to the previous survey are linked for calculations of before-and-after changes in their intention to use research evidence. We will follow up with participants who do not complete the survey once per week for three weeks to minimize the number of participants lost to follow up.

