For all analyses, we will use the intention to treat principle, report 95% confidence intervals, and consider p-values equal to or less than 0.05 (two-tailed) to be significant. For the primary outcome measure (mean logins/month/organization), missing data are irrelevant as they are a naturalistic measure. For the secondary outcome measure (obtained through the survey), missing data can be taken into account through the use of a mixed-effects model.

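### Organizations are allocated at the start of a two-month baseline period in which both arms get the same service, so any that leave in those months become avoidable post-randomization losses

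*Protocol article*

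**What the plan says.** The Randomization section of the protocol article says: "After consenting to participate in the trial, we will use simple randomization to assign organizations to receive either" of the two versions. The assignment is made in one run from a list of participating organizations, with equal numbers per arm. The result then goes to the database administrator. The same section says that the statistician "will only be involved with randomization at the start of the trial and the data analysis upon completion of the trial".

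Methods/design describes a 10-month trial, "which includes a two-month baseline period where all participants receive the 'self-serve' evidence service". The arms differ only in the six months after that.

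Study population and recruitment says "we require one key organizational decision maker to fill out a brief survey measuring their intention to use research evidence", at baseline and again at completion. Outcomes gives the timing: "We will administer the instrument to one key decision maker from each organization during the baseline period", and again at the end of the six-month intervention period. Those who do not respond are reminded weekly for three weeks.

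The RCT section on data management and analysis applies intention to treat to all analyses. For the login outcome it states that "missing data are irrelevant as they are a naturalistic measure"; missing survey data are left to a mixed-effects model. Statistical precision assumes login data from every organization, with no allowance for loss.

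**The concern.** The 10 months include the baseline period, so the start of the trial is the start of baseline. Allocation therefore comes two months before the arms differ. The documents name no baseline task that depends on it and give no reason for allocating so early.

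An organization that closes or withdraws in those two months has been randomized but can never receive the service it was allocated to. That leaves two unattractive choices:

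- **Keep it.** This honours intention to treat. If its logins count as zero, it cannot show a treatment effect and pulls the difference between arms towards zero.
- **Drop it.** This is an exclusion after randomization, contrary to the stated principle, and may leave the arms unequal by chance.

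The trial can ill afford either. It expects about 42 organizations per arm, and its Discussion names the small sample as the main limitation.

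**Working it through.** **Inputs from the protocol article (Statistical precision):** 42 organizations per group, six monthly measurements, SD 1.0, 80% power, two-sided 0.05, ICC 0.2 to 0.8. I use 84 organizations in total (70% of 120, or 2 × 42); the text rounds this to about 85.

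**Assumption:** a fraction f of organizations leaves completely during baseline. The documents give no value, so I show 2%, 5% and 10%.

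**Step 1: reproduce the plan's figures.** The time-averaged detectable difference is d = (1.960 + 0.842) × √[2(1 + 5 × ICC) / (6 × 42)]. For ICC 0.2 this is 2.802 × √(4/252) = 0.353. For ICC 0.3, 0.5, 0.7 and 0.8 it is 0.395, 0.467, 0.529 and 0.558. The plan states 0.35, 0.39, 0.47, 0.53 and 0.56. The figures reproduce, given zero loss.

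**Step 2: randomize early, keep leavers as zero logins.** The average effect shrinks to (1 − f) times the effect among those who stay, while the sample stays at 84. With the SD held at 1, the equivalent undiluted sample is 84 × (1 − f)², the detectable effect among stayers is d/(1 − f), and power at the no-loss difference is Φ[2.802(1 − f) − 1.960].

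**Step 3: randomize after baseline.** Leavers never enter, so there is no dilution. The sample is 84 × (1 − f), the detectable effect is d/√(1 − f), and power is Φ[2.802√(1 − f) − 1.960].

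| f | Organizations lost | Effective sample, early / late | Detectable effect at ICC 0.2, early / late | Power, early / late |
|---|---|---|---|---|
| 2% | 1.7 | 80.7 / 82.3 | 0.360 / 0.357 | 78.4% / 79.2% |
| 5% | 4.2 | 75.8 / 79.8 | 0.372 / 0.362 | 75.9% / 78.0% |
| 10% | 8.4 | 68.0 / 75.6 | 0.392 / 0.372 | 71.3% / 75.7% |

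Late randomization does not stop organizations leaving. Its gain is the difference within each pair: 84 × f × (1 − f) = 1.6, 4.0 and 7.6 effective organizations.

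**Step 4: who counts towards f.** Only complete exits do. An organization that skips the baseline survey still has users, logins and exposure to its allocated service, so its primary-outcome data are intact. The mixed-effects model can also use its follow-up score.

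**The case against.** The strongest reply is that randomizing before a common period is valid under intention to treat, and no bias has been shown. Both arms have the same service in those months and participants are described as blinded, so exits should not depend on arm. This stands, and it limits the point to precision and a clean analysis set.

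Dilution is not certain even for complete exits. The outcome averages logins over an organization's users, and staff changes are tracked by regular emails. An organization with no users left has an undefined value, not a zero. That also stands: Step 2 applies only if such organizations are scored as zero. If they are dropped instead, precision is about the same as with late randomization, but through a post-randomization exclusion. The detailed scoring rule may properly sit in a fuller document. The timing of randomization is fixed here.

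The order is also inferred from two sections and is not stated in one sentence. If allocation is in fact run at the switch, clearer wording is all that is needed.

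Stronger readings are tempting, and the documents do not support them:

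- **Survey non-completers as losses.** A reader might infer this because the survey is required yet comes after allocation. Step 4 shows why it does not follow. The planned reminders reduce non-completion further.
- **Survey completion as a condition of randomization.** If 10% missed the survey but kept logging in (an assumption), the condition would cut the primary analysis from 84 to about 76 organizations and raise the detectable difference at ICC 0.2 from 0.353 to 0.372. It would discard usable data.
- **Compromised concealment.** The administrator holds the allocation during baseline, but is external to the research team, and allocation follows consent. Enrolment cannot be steered this way.
- **Many organizations naming no users.** User lists are requested before the trial starts, so this route is largely closed.

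**Conclusion.** The point holds as a modest design improvement. The stated order puts allocation two months ahead of any difference between the arms, for no stated reason, and so turns complete exits during baseline into post-randomization losses.

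The size depends on an exit rate that the documents do not give. Over an assumed 2% to 10%, with leavers scored as zero and the SD unchanged, the effective sample is about 81 to 68 of 84 with early randomization and 82 to 76 with late. At 2% the difference is negligible; at 10% it is about four percentage points of power. For a complete-case survey analysis, power would be about the same either way. The plan's precision figures are correct on their own zero-loss assumption.

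**What to change.** Change the Randomization section so that the same single-list, equal-number randomization is run at the end of the two-month baseline period, just before the intervention arm is switched to full-serve. Include every organization that is still participating and has at least one registered user. Send the allocation list to the database administrator only then, and define the intention-to-treat set as all organizations randomized at that point.

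Request the baseline survey before randomization, with the reminders already planned, but do not make its completion a condition.

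The cost is small. The trial's length, baseline data and final two-month period are unchanged, and the intervention arm has to be switched at month two in any case. The randomized number falls by the organizations that leave during baseline, and the administrator has less lead time to set up full-serve access.

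If early randomization is kept, the protocol should give the reason, say how organizations that leave during baseline are analysed, and allow for loss in the Statistical precision section.

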### Data management and analysis

Data will be entered into SPSS 16.0 using unique identifiers that link each participant to their respective organizational identifier assigned during the randomization process. Analyses will be conducted by two members of the team ([name] and TB) and, during the analysis, all investigators -- except for one of us who is involved in the both the analysis and randomization (TB) -- will be blinded to the key linking the organizations to their unique identifiers.

We will treat both outcome measures as continuous variables and analyze the change in these measures over time using a two-way mixed effects linear repeated measures analysis of variance (ANOVA), which will assess the effects within groups, between groups, and over time with the latter as the main feature of interest. In addition, we will control for four variables -- province the organization is located in, size of organization (as measured by number full-time equivalent staff in the organization), number of participants that participated from each organization, and the number of clients served each year by the organization -- using analysis of covariance. For the analysis of the secondary outcome, we will also control for whether the key decision maker is full-time or part-time, and whether they have had research training in the past. Each of these variables may at least partially explain research use (*e.g.*, the amount of staff support an executive director or manager has may determine the extent to which they can spend time finding and using research evidence), and therefore adjusting for them will allow for a better assessment of the effects of the intervention. Moreover, as part of a secondary analysis, we will assess whether there is an interaction between each (entered as fixed factors) and the outcome measures. Given the likelihood that the distribution of the outcomes will be skewed, we will transform the data where necessary and possible, which may include adjusting the time period for which we calculate the mean number of logins/month/organization (*e.g.*, calculating the mean over two months) if the number of logins is low and there are insufficient data for analysis. We will also qualitatively compare the number of participants in the intervention and control groups that do not complete the follow-up survey, and attempt to assess if there are reasons for why they dropped out based on their baseline characteristics.

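### Participant blinding is claimed but cannot hold, at least in the full-serve arm, and one of the two analysts knows allocation while key analysis choices remain open

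*Protocol article*

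**What the plan says.** The Randomization section concludes: "Therefore, participants and all investigators except the statistician" and the SHARE database administrator "will be blinded to group assignment". The preceding sentence gives the reason: the statistician, a member of the study team, "will only be involved with randomization at the start of the trial and the data analysis upon completion of the trial". The same section has this statistician assign the organization IDs, randomise, and keep both the ID key and the randomization log. It also says that the administrator, who is outside the research team, will need the key, and that the key stays concealed from the research team.

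Methods/design sets out the exposure: "a two-month baseline period where all participants receive the 'self-serve' evidence service", then "a six-month period where the intervention group will receive the 'full-serve' evidence service" while controls stay on self-serve. Table 1 and the two arm descriptions give the difference between the versions. Self-serve is a list of reviews by publication year, with links and worksheets. Full-serve adds a searchable database, email updates at least monthly, user-friendly summaries, usefulness ratings, a comment facility and full-text links.

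The RCT section on data management and analysis names two analysts, one of them the statistician. It says that the other investigators "will be blinded to the key linking the organizations to their unique identifiers". It allows the outcomes to be transformed where needed and the login-averaging period to be changed if logins are sparse.

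**The concern.** A reader who takes the blinding sentence at face value will judge the survey result as if respondents did not know which service they had. That matters because the secondary outcome is intention to use research evidence, self-reported by one decision maker per organization. An intervention-arm respondent who has watched a new and richer service arrive may report stronger intention for that reason alone. The Discussion lists sample size and contamination as limitations and does not mention lack of blinding, so nothing elsewhere corrects the impression.

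The second issue is in the analysis. The averaging window and the transformation of the primary outcome can both move the result. The text leaves them to be decided once the data are seen, by a team in which one of the two analysts holds the allocation.

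**Working it through.** The blinding claim has no figure to recompute. The protocol's precision figures concern the detectable difference in logins and do not bear on it. The check sets the sections against each other.

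1. **Does the stated reason support the claim?** The sentence is drawn as an inference from the limits on the statistician's role. Those limits can restrict what investigators learn. They have no bearing on what a user sees on the website or in an inbox, so the conclusion about participants does not follow.

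2. **What does an intervention-arm user see?** In months 1–2, a list of reviews by year. From month 3, a search interface, summaries, ratings, comments, full-text links and at least one email a month. Each user has a direct before-and-after comparison. Nothing in the article says that the versions are made to look alike or that the switch is disguised.

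3. **What does a control-arm user see?** The same self-serve listing through month 8, then full-serve in months 9–10. The Outcomes section places the follow-up survey at the end of the six-month intervention period, before controls see any change. (The recruitment section instead speaks of completion of the trial. If that meant month 10, controls too would have seen a switch before answering. The Outcomes wording is the more specific and is used here.)

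4. **How many are affected?** 0.70 × 120 = 84 organizations, or 84 / 2 = 42 per arm; the protocol works with about 85 in total and 42 per group. With one survey respondent per organization, about 42 respondents, the whole intervention arm, cannot be regarded as blinded.

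5. **Which outcome is exposed?** Intention is self-reported, so both the answer and its measurement are exposed. Logins are recorded by the server through user accounts, so their measurement is protected. How often people log in can still respond to knowing which version they have.

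6. **Who knows allocation at analysis?** One of the two analysts, by the protocol's own account. The open choices are the transformation and the averaging window. The covariates are already listed and are not open in the same way.

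7. **Is the concealment statement consistent?** The key is said to be concealed from the research team, yet it is kept by someone whom the same section calls a member of the study team. The later exception for the statistician shows what is probably meant, but the two statements do not agree as written.

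**The case against.** The strongest reply is that most of the blinding statement survives. Four points stand.

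- A reader might infer that the statistician's dual role refutes the claim. It does not: the exception is disclosed in both the Randomization section and the analysis section. It is an acknowledged weakness, not a contradiction.
- A reader might infer that the other investigators are blinded only to organization identity and can see the arm. The Randomization section claims blinding to group assignment for them, and an administrator outside the team grants access and sends the updates. Usage items that exist only under full-serve, such as email forwards and summary views, could reveal the arm. However, they are listed as descriptive measures, and the article does not say that they reach the second analyst before the primary analysis. Leakage is possible but not shown.
- A reader might infer that all survey respondents are unblinded. Controls see no change before the six-month survey, and what they were told about the comparison is not visible here. The argument is firm only for the intervention arm.
- The article does not say which analyst would choose the window or transformation, and the window change is conditional on sparse data. It is therefore not established that the unblinded analyst makes these choices, only that nothing in the text prevents it.

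None of this rescues the statement about participants. Allocation concealment is not in question, because organizations consent before the list is randomised.

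**Conclusion.** The claim that participants are blinded is contradicted by the protocol's own schedule and intervention description, at least for the intervention arm (about 42 organizations). The intention outcome should be treated as open to expectation bias. The document gives no basis for the size of that bias, and none is asserted here. The conclusion assumes that the two versions look as different as Table 1 and the arm descriptions indicate, and that the survey falls at six months.

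On the analysis side, the finding is a disclosed but avoidable exposure: one of two analysts knows allocation while two influential choices are left to the data. The statement about concealment of the key needs reconciling. It would be wrong to conclude that no blinding exists. The blinding of the other investigators is not shown to fail, and the measurement of logins does not depend on it. The trial remains workable; the statement should be corrected and the analysis choices protected.

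**What to change.** - In the Randomization section, delete the claim for participants and say that they are not blinded to the service they receive. State for each role (statistician, administrator, second analyst, other investigators) what that person does and does not know: arm, organization identity, or both.
- Reconcile the statement that the key is concealed from the research team with its being kept by a study-team member.
- In the Discussion and in reporting, describe the intention result as unblinded self-report. Describe logins as protected in measurement but not from users' behaviour.
- Have the database administrator supply organization-level logins with arms coded A/B and without the usage fields that exist only under full-serve. Have the second analyst fix and record the averaging window and the transformation on these data before the code is broken.

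The cost is a few sentences and a small amount of extra data handling. The administrator and the second analyst are already in place; the plan assumes that the second analyst can make these two choices competently, which the article does not show.
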